# Outcome of Critically ill Patients Undergoing Mandatory Insulin Therapy Compared to Usual Care Insulin Therapy: Protocol for a Pilot Randomized Controlled Trial 

**DOI:** 10.2196/resprot.5912

**Published:** 2018-03-08

**Keywords:** intensive care, insulin, glycaemic control

## Abstract

**Background:**

Observational and interventional studies in patients with both acute medical conditions and long-standing diabetes have shown that improved blood glucose control confers a survival advantage or reduces complication rates. Policies of “tight” glycaemic control were rapidly adopted by many general intensive care units (ICUs) worldwide in the mid 00’s, even though the results of the studies were not generalizable to mixed medical/surgical ICUs with different intravenous feeding policies.

**Objective:**

The primary objective of the study is to assess the safety of mandatory insulin infusion in critically ill patients in a general ICU setting.

**Methods:**

This protocol summarizes the rationale and design of a randomized, controlled, single-center trial investigating the effect of mandatory insulin therapy versus usual care insulin therapy for those patients admitted for a stay of longer than 48 hours. In total, 109 critically ill adults predicted to stay in intensive care for longer than 48 hours consented. The primary outcome is to determine the safety of mandatory insulin therapy in critically ill patients using the number of episodes of hypoglycaemia and hypokalaemia per unit length of stay in intensive care. Secondary outcomes include the duration of mechanical ventilation, duration of ICU and hospital stay, hospital mortality, and measures of renal, hepatic, and haematological dysfunction.

**Results:**

The project was funded in 2005 and enrolment was completed 2007. Data analysis is currently underway and the first results are expected to be submitted for publication in 2018.

**Conclusions:**

This protocol for a randomized controlled trial investigating the effect of mandatory insulin therapy should provide an answer to a key question for the management of patients in the ICU and ultimately improving outcome.

**Trial Registration:**

International Standard Randomized Controlled Trial Number ISRCTN00550641; http://www.isrctn.com/ISRCTN00550641 (Archived at WebCite: http://www.webcitation.org/6xk8NXxNv).

## Introduction

### Background

Observational and interventional studies in patients with both acute medical conditions and long-standing diabetes have shown that improved blood glucose control confers a survival advantage or reduces complication rates [1-4]. In 2001, Van den Berghe and colleagues extended this to critically ill patients with no history of diabetes when they published the results of a study of “tight” blood glucose control compared with conventional blood glucose control in Dutch intensive care unit (ICU) patients following surgery [5]. They showed a corrected relative reduction in intensive care mortality of 32% in the “tight” control group, with the benefits primarily seen in the patients who required a prolonged ICU stay. A reduced ICU length of stay and a reduction in the incidence of renal dysfunction and nosocomial infections were also seen in the “tight” glucose control patients.

Tight glycaemic control therapy necessitates increased insulin administration to achieve euglycaemia. This raises the possibility that any patient benefits may be a result of the insulin delivered rather than the glycaemic control attained, and that further improvements in patient outcomes might be possible with increased insulin administration [6]. However, intensive insulin therapy is a complex intervention. The effects depend upon the protocol used, feeding strategies, staff training and availability, and the method of near-patient glucose concentration measurement used. Separation of the effects of insulin infusion from those of euglycaemia could be achieved by comparing two groups receiving substantially different quantities of insulin, but achieving similar glycaemic control. However, mandatory continuous insulin infusion (to achieve higher insulin infusion rates than those required simply for glycaemic control) has not been undertaken in ICU patients for the prolonged periods utilized in studies of tight glycaemic control, although previous studies have shown much higher insulin rates to be safe in intensive care patients over short periods [7-9]. This trial aims primarily to determine if insulin infusions of 96 units/day can be achieved safely in a UK mixed general adult ICU, and what short-term biochemical effects occur with these infusions.

### Mechanisms by Which Insulin Might Alter Intensive Care Unit Mortality

Whilst it has long been known that chronic derangements of lipid profile are associated with long-term increases in mortality, more recent studies in the critical care environment suggest they also have an impact on acute survival [10]. The lipid profile of the critically ill patient is frequently abnormal, most commonly showing increased triglycerides combined with low levels of high-density lipoproteins (HDLs) and low-density lipoproteins (LDLs) cholesterol. This is partly due to the insulin resistance caused by acute illness or trauma. Observational studies suggest that the severity of these abnormalities correlate with an increased mortality [11].

By inhibiting hormone-sensitive lipase, insulin would be anticipated to decrease free-circulating triglycerides, which have been linearly correlated with mortality [12]. Excess triglycerides are thought to be toxic to the cell membrane and also increase oxygen consumption in an already ischemic environment.

Conversely, there is a body of animal work and some human studies that suggest that hypertriglyceridaemia is protective in gram negative sepsis because triglyceride-rich lipoproteins absorb endotoxin, thus preventing CD14 positive monocyte mediated cellular activation [13].

It may be that insulin, whilst reducing the amount of triglyceride available to absorb endotoxins, increases absorption by other mechanisms. It has been shown to ameliorate the decrease serum HDL levels in the critically ill. HDL has been shown to absorb the majority of endotoxins incubated with whole blood, and infusing reconstituted HDL has been shown to prevent endotoxin stimulated TNF-α production [14]. Moreover, HDL has been shown to provide endothelial protection by both antiapoptotic and antioxidative mechanisms [15].

Initially, this work seems contradictory to retrospective studies which showed a decreased mortality and incidence of sepsis in patients treated with long-term (lipid-lowering) 3-hydroxy-3-methyl-glutaryl-coenzyme A (HMG CoA) reductase inhibitors (statins) prior to their critical illness [16,17]. However, whilst reducing LDL cholesterol, statins, in common with insulin, cause moderate elevation of serum HDL [18]. The above mechanisms may therefore be similarly applicable, as statins are also known to have a range of other anti-inflammatory actions [19].

Critical illness is associated with increased protein catabolism that is relatively resistant to nutritional support [20]. The consequent loss of skeletal muscle leads to respiratory muscle weakness and a prolonged need for mechanical ventilation [21,22]. Small studies, mainly of burn patients, suggest insulin causes a decrease in protein catabolism, but have not shown morbidity or mortality benefits [23-25]. Work has suggested that the negative nitrogen balance that occurs is partly attributable to growth hormone resistance and decreased production and action of insulin-like growth factor 1 (IGF-1) [21]. Administration of high levels of growth hormone has been shown to improve nitrogen balance, but two large European randomized trials demonstrated increased mortality rates in the critically ill [26]. This was thought to be due to a combination of immunomodulatory and hyperglycaemic effects. Many of the effects of growth hormone are mediated via insulin-like growth factors (formerly somatomedins), modulation of which may avoid these unwanted effects.

Infusion of exogenous insulin into volunteers causes an increase in IGF-1 by inducing a reduction in the concentration of its binding protein insulin-like growth factor binding protein 1 (IGFBP-1) [27]. Serum IGF-1 levels have been consistently reported as low in acutely ill patients [28-31] and high IGFBP-1 levels have been associated with increased mortality in similar patients [32]. A longitudinal study of 18 heterogeneous critically ill patients showed initially low-circulating concentrations of IGF-1 and increasing IGF-1 values on recovery [33]. IGF-1 is both antiapoptotic and anabolic, and so might reduce the muscle wasting that leads to prolonged ventilator dependence. The vast majority of insulin-like growth factors in the circulation exist in a ternary complex with IGFBP-3 and an acid-labile subunit (ALS). This complex is too large to traverse the capillary endothelia and stimulate insulin or IGF receptors. ALS is also essential in sustaining plasma levels of IGF’s as it extends their half-life from 10 minutes to twelve hours. Levels of ALS are reduced in critical illness due to growth hormone and insulin resistance. The effect of mandatory insulin infusion on these aspects of the somatotrophic axis in the critically ill is unknown. Work from a subgroup of the original Van den Berghe trial has, somewhat surprisingly, shown a decrease in IGF-1 in the “tight glycaemic control” arm of the study [19].

The overall results of all these studies would seem to indicate that there may be a benefit from “tight glycaemic control”. A trial designed to clearly delineate insulin dose between two arms should provide more evidence for the science behind this new “therapy” if this feasibility trial can show that recruitment of ICU patients is possible and the therapy is shown to be able to be delivered safely.

### Objectives

The primary objective of the study is to determine the safety of mandatory insulin infusion in critically ill patients in a general ICU setting. This will be assessed by the number of episodes of hypoglycaemia and hypokalaemia per unit length of stay in intensive care.

The secondary objectives are to investigate four mechanisms by which exogenous insulin might alter outcome: (1) effects on lipid profiles (to include free fatty acids profiles, triglyceride, HDL, and LDL levels); (2) effects on nitrogen balance; (3) effects on the somatotrophic axis; and (4) effect on oxidative damage by measuring protein carbonyls.

## Methods

### Trial Design, Setting, and Patient Population

This is a randomized, controlled, open-label, single-centre trial comparing two strategies for the management of blood glucose in the ICU. The study will be conducted in one General (noncardiac) ICU at a UK university teaching hospital. All patients admitted to the ICU will be screened for eligibility. The study sponsor is the Oxford University Hospitals NHS Trust. A SPIRIT figure showing the schedule of enrolment, assessment of outcome measures, allocation, and interventions is shown in Figure 1. Those that were not diabetic, had not had hepato-biliary surgery or had a diagnosis other than pancreatitis, and who were expected to stay in the ICU for at least 48 hours were eligible for inclusion. The full inclusion and exclusion criteria is listed in Textbox 1.

**Figure 1 figure1:**
[figure not shown]
SPIRIT flowchart.

Inclusion and exclusion criteria.Inclusion criteria:16 years or olderDeemed by the attending physician to require 48 hours or more days of critical care treatmentExclusion criteria:Known diabetes mellitusAdmitted with diabetic ketoacidosisCurrent diagnosis of pancreatitisUndergone hepato-biliary surgery in the current admissionInsulinoma or pituitary tumourCurrently on, or likely to require, total parenteral nutritionPregnant or breast-feedingPrimary diagnosis of head injuryPrimary diagnosis of intracranial haemorrhagePrimary diagnosis of strokeInclusion in another studyCurrently placed under a section orderLearning disabilityUnable to speak English and without a suitable translatorAlready on higher than 4 units of insulin per hour and have been so for at least 3 out of the last 24 hoursNo central line accessHad cranial neurosurgery within the past 4 weeksSpent more than 24 hours on another ICU directly before this ICU admissionPrisonersUndergone kidney-pancreas transplant in the current admissionFailure to synthesise glucose

### Study Definitions

*Hypoglycaemia* is defined as a blood glucose measurement taken that is less than 2.2 mmol/L (this low level is set to be in agreement with other completed and in-progress trials [5,34-38]). *Hypokalaemia* is defined as a blood potassium measurement taken that is less than 2.6 mmol/L.

### Treatment

#### Line Management for Both Arms

A central line port should be dedicated to study use (as well as with Total Parenteral Nutrition). This port can be used for both insulin and glucose infusions. Both insulin and glucose infusions need priming (2 mls) for central infusion.

#### Potassium Measurement and Monitoring

Serum potassium should be monitored at least every 4 hours (by blood gas analysis or laboratory).

#### Mandatory Insulin Therapy (Intervention Arm)—4 Units of Actrapid Insulin Infusion per Hour

As soon as possible after randomization, an infusion of Actrapid (Novo Nordisk) should be prepared (50 units of Actrapid should be made up to 50 mls with 0.9% normal saline). This should be attached to an infusion pump to enable the patient to receive a mandatory insulin infusion of 4 units of Actrapid per hour. The syringe should be changed every 24 hours. A bag of 50% glucose should also be set up and the rate of this infusion is as per Table 1 to maintain normoglycaemia. Normoglycaemia will be maintained by sliding scale 50% glucose infusion with the rate of glucose infusion being dependent upon the blood glucose measurement as per Table 1.

If a patient has blood glucose measurements greater than 8 mmol/L after initial stabilisation (meaning the first 5 hours of treatment, or after initiation or change of feeding) on 3 successive occasions after stopping glucose infusion, they should be transferred to standard (insulin sliding scale) treatment. It should be checked that nutrition is not being given incorrectly prior to this decision being made.

**Table 1 table1:** 50% glucose infusion rates for mandatory insulin therapy arm

Blood glucose measurement (mmol/L)	Glucose infusion rate
<2.6	Stop insulin infusion Bolus patient with 25ml of 50% glucose Seek medical advice Repeat blood glucose measurement in 30 minutes Once the blood glucose is back in the normal range the insulin infusion should be recommenced with the 50% glucose solution infusion rate increased by 8 mls per hour
<4.1	Increase 50% glucose infusion rate by 8 mls per hour Measure blood glucose again in 30 minutes
4.1 – 7	No change to infusion rate Measure blood glucose again in 60 minutes^a^
>7	Decrease 50% glucose infusion rate by 4 mls per hour Measure blood glucose again in 60 minutes^a^

^a^If blood glucose levels are changing rapidly, more frequent measurements may be necessary. If blood glucose levels remain in the desired range (and do not alter by more than 0.7 mmol/L each time) for 2 consecutive hours without alteration of glucose infusion, blood glucose measurement may be reduced to 2 hourly.

**Table 2 table2:** Insulin infusion rates for usual care insulin therapy arm.

Blood glucose measurement (mmol/L)	Insulin infusion rate (units per hour)
0 – 4	0.5
4.1 – 7	1.0
7.1 - 11	2.0
11.1 – 17	4.0
17.1 – 27	7.0
>27	10.0

If changes to a patient's feed- or glucose-containing intravenous fluid regimes occur or if a feeding break occurs, hourly monitoring of blood glucose should be recommenced until the levels are again stable. Immediately after the stopping of feed, increase the glucose infusion rate by 8 mls per hour.

As soon as it is known a patient will be discharged the patient should have both glucose and insulin stopped. A blood gas (arterial or venous) should be taken just prior to departure to check that blood glucose and potassium levels are within the normal range.

#### Usual Care Insulin Therapy (Control Arm)

Only the frequency of blood glucose and potassium monitoring was changed for these patients (to be more frequent, every hour) and the standard unit guidelines for insulin administration should be followed. Actrapid should be made up as per the treatment arm. The unit guidelines are for the target range of 4-7 mmol/L blood glucose which should be achieved with insulin doses as per Table 2.

#### Therapy Administration

Once a patient is entered into the trial, either the patients’ attending nurse, the trial physician, or research nurse will set up the assigned therapy. The patients nurse will then follow either Table 1 or Table 2, depending upon allocation, to adjust the insulin and glucose infusions accordingly. As per the unit protocol and trial protocol, a physician should be called for any patients that has a blood glucose measurement of less than 2.6 mmol/L and the patient must be treated immediately for hypoglycaemia.

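### Table 2 keeps insulin running at readings that other sections treat as hypoglycaemia, and the high-glucose transfer rule leads to an equal or lower insulin rate for readings up to 17 mmol/L

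*Protocol article*

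**What the plan says.** Therapy Administration makes the allocated table the working instruction: "The patients nurse will then follow either Table 1 or Table 2, depending upon allocation, to adjust the insulin and glucose infusions accordingly". It then adds a rule for both arms, under which a physician is called for any patient with a "blood glucose measurement of less than 2.6 mmol/L and the patient must be treated immediately for hypoglycaemia".

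In the mandatory arm, Table 1 has its own row below 2.6 mmol/L: "Stop insulin infusion Bolus patient with 25ml of 50% glucose Seek medical advice", followed by a repeat measurement at 30 minutes. Table 2, titled "Insulin infusion rates for usual care insulin therapy arm", has no such row. Its lowest band is 0-4 mmol/L at 0.5 units/h, with no stop instruction and no pointer to the rule in Therapy Administration. The Usual Care section sets hourly monitoring and a "target range of 4-7 mmol/L blood glucose which should be achieved with insulin doses as per Table 2".

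At the other end, a mandatory-arm patient who reads above 8 mmol/L after initial stabilisation is covered by this rule: "on 3 successive occasions after stopping glucose infusion, they should be transferred to standard (insulin sliding scale) treatment". The Discussion says that the design depends on comparable glucose control in the two groups with unequal insulin doses.

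**The concern.** Study Definitions sets hypoglycaemia at below 2.2 mmol/L, so every control-arm hypoglycaemic event lies inside the one Table 2 row that keeps insulin running. A nurse reading Table 2 alone and a nurse reading Therapy Administration are not told the same thing. The mandatory-arm nurse has a detailed sequence in Table 1. In an open-label trial whose primary outcome includes the number of hypoglycaemic episodes, what is done after a low reading, and how soon glucose is measured again, can affect what is counted.

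The transfer rule raises a different question. It applies to patients whose glucose stays high on 4 units/h with the glucose infusion already stopped, yet the receiving scale gives many of them less insulin and none of them more until glucose exceeds 17 mmol/L. Under intention to treat they remain in the mandatory group. The insulin contrast between the groups is therefore diluted, and the similarity in glucose may be too.

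**Working it through.** **Inputs.** The mandatory rate is 4 units/h (Mandatory Insulin Therapy section). The stated daily dose is 96 units (Background). The transfer trigger is above 8 mmol/L (Mandatory Insulin Therapy section). The treatment threshold is below 2.6 mmol/L (Therapy Administration). The endpoint threshold is below 2.2 mmol/L (Study Definitions). Rates by glucose band are from Table 2.

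**The plan's own figure.** 4 units/h x 24 h = 96 units/day, which reproduces the stated dose.

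**Low readings, side by side.**

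| Reading (mmol/L) | Table 1 (mandatory) | Table 2 (usual care) | Therapy Administration (both arms) |
|---|---|---|---|
| Below 2.6 | Insulin stopped, glucose bolus, advice sought, repeat at 30 min | 0.5 units/h | Physician called, immediate treatment |
| 2.6 to 4.0 | Glucose infusion increased, repeat at 30 min | 0.5 units/h | No specific rule |

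At 1.5, 2.1 and 2.5 mmol/L, Table 2 returns 0.5 units/h each time (0.5 x 24 = 12 units/day if held). Therapy Administration does not say whether control-arm insulin stops, nor when glucose is measured again. The written interval for controls remains hourly.

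**What the intervals do to a count.** During one hour spent below 2.2 mmol/L, 30-minute repeats give 60/30 = 2 further readings and hourly repeats give 60/60 = 1. If each low reading were counted, the same hour would add twice as many repeat readings in the mandatory arm. If consecutive low readings are counted as one episode, this difference disappears. Working the other way, insulin continued in a control patient could allow a further low reading after partial recovery. The documents give no data to weigh one against the other.

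**Transfer from 4 units/h, taking the standard sliding scale to be Table 2.** Change = (Table 2 rate - 4) / 4.

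| Reading (mmol/L) | Table 2 rate (units/h) | Units/day if held | Change |
|---|---|---|---|
| Above 8 to 11 | 2.0 | 48 | (2 - 4)/4 = -50% |
| 11.1-17 | 4.0 | 96 | (4 - 4)/4 = 0% |
| 17.1-27 | 7.0 | 168 | (7 - 4)/4 = +75% |
| Above 27 | 10.0 | 240 | (10 - 4)/4 = +150% |

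The band with the reduction begins at the trigger itself, so a patient transferred with readings just above 8 mmol/L moves to half the previous rate.

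**The case against.** On low readings, the strongest reply is that Therapy Administration already supplies a common rule. It covers any patient, follows directly after the instruction to use the tables, and can be read as overriding Table 2. It also refers to the unit protocol, which is not shown and may contain the unit's hypoglycaemia procedure. This stands in part: a common duty to treat is written down, and nothing shows that control patients were left on insulin while hypoglycaemic. But the override is not stated, Table 2 has no exception, and the detail on stopping insulin and re-measuring is printed for one arm only.

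A reader might infer that longer control-arm hypoglycaemia makes mandatory insulin look safer. The documents do not support that direction. The primary outcome counts episodes or events, not their duration; the immediate-treatment rule covers both arms; and the shorter repeat interval in the mandatory arm could raise that arm's count instead.

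On transfer, it is fair to say that the rule nowhere promises more insulin. It is an exit to usual care, and transferred patients join the controls' own scale. A reader might infer that Table 2 contradicts the protocol at both ends, but that is too strong. The reduction lies in a mid-table row, and at the top of the table insulin rises. What remains is an incoherence: the rule responds to high glucose on 4 units/h by assigning the same rate or less up to 17 mmol/L.

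**Conclusion.** Two points stand. First, Table 2 as printed does not fit the immediate-treatment rule or Table 1 for any reading below 2.6 mmol/L, a range that contains every control-arm hypoglycaemic event. The arms therefore have different written handling of a primary-outcome component. The size and direction of any effect on the episode count are unknown.

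Second, the transfer rule sits badly with the glucose target and with the comparable control that the Discussion requires: -50% insulin above 8 and up to 11 mmol/L, no change at 11.1-17, and an increase only above 17. This rests on reading the standard sliding scale as Table 2. The Usual Care section supports that reading by tying the standard unit guidelines to Table 2, but the transfer rule does not name the table. The number of patients transferred is not given, so the effect on the group comparison cannot be sized, and a loss of the glucose match is a possibility rather than a finding.

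**What to change.** Reconcile Table 2's lowest row with Therapy Administration and Table 1, and reconcile the transfer rule with Table 2's 7.1-11 and 11.1-17 rows. Which rule or rate is right is for the clinical team, not this review. Enrolment was completed in 2007 and follow-up is finished, so this means a clear statement in the report of which instructions applied; it cannot change care.

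The Data Collection section says that all glucose values and the insulin and glucose doses are recorded. From these, report by arm:

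- the insulin rate running at each reading below 2.6 mmol/L and the interval to the next measurement;
- the time to recovery, with one recovery threshold for both arms, noting that the written schedules resolve it only to 30 minutes in one arm and 60 in the other;
- the number of mandatory-arm patients transferred, with their glucose and insulin rates before and after.

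Count hypoglycaemic episodes by one rule in both arms, so that repeat readings within an episode are not counted as new events, and interpret the primary comparison in the light of these tables. The cost is a few extra descriptive tables and no new data collection.
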